#### Quantitative analysis: phase IIa

2.3.3

Descriptive statistics will be used to summarize participant characteristics and feasibility and acceptability outcomes. Changes in exploratory behavioral and biomedical outcomes between baseline and post-intervention will be analyzed using paired-samples *t*-tests, Wilcoxon signed-rank tests, or McNemar's tests, as appropriate. Exploratory analyses will examine associations between dietary adherence scores and biomedical indicators (HbA1c and anthropometric measures) to assess convergent validity. All analyses will be conducted using Stata (version 19; StataCorp LLC, College Station, TX, USA), with statistical significance set at *P* < 0.05.

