### Phase IIa: proof-of-concept

2.3

Phase IIa will be conducted following completion of Phase Ib, as findings from the refinement phase are essential to determine the readiness of the OSanDiaBé intervention for feasibility testing. Consistent with the ORBIT framework, the primary objective of Phase IIa is to assess the feasibility and acceptability of the culturally tailored, dietitian-led MNT intervention using a mixed-methods design. We hypothesize that key feasibility indicators, including recruitment, retention, and session attendance, along with participant satisfaction and acceptability, will exceed 75%, indicating readiness for pilot testing in Phase IIb.

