#### Phase IIa sample

2.3.1

A single-arm feasibility design will be used to enroll 30 adults with T2D. Eligible participants will (1) self-identify as Beninese; (2) be aged 40–65 years; (3) have a clinical diagnosis of T2D for at least one year; (4) have an HbA1c level >7% at enrollment; (5) have a family member willing to participate or provide ongoing support; and (6) be willing to commit to the study protocol and attend scheduled sessions. Participants will be recruited from the pool of 512 individuals who participated in Phase Ib. The sample size of 30 was selected in accordance with recommendations for pre-pilot and feasibility studies (43). The intervention will include two individual sessions (45–60 min each) and eight group sessions (90–120 min each). Sessions will be delivered by six trained dietitians or nutritionists, with each group of 10 participants assigned two facilitators experienced in health promotion, trained in MNT, and committed to maintaining protocol fidelity.

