**Figure 3 F3:**
[figure not shown]
Schematic diagram of the feasibility study for the new cultural tailored medical nutrition therapy.

To support future replication and scalability, feasibility and acceptability outcomes will be evaluated using the RE-AIM (Reach, Effectiveness, Adoption, Implementation, and Maintenance) framework (52). Feasibility indicators will include recruitment strategies, session attendance, retention rates, and facilitator fidelity assessed through session observations. Acceptability will be measured using participant-reported perceptions of cultural relevance, perceived benefits, and overall satisfaction. Although Phase IIa is not designed to test efficacy, exploratory assessments of behavioral and biomedical outcomes will be conducted at baseline and 12 weeks post-intervention. Dietary adherence will be assessed using a multi-method approach combining the Perceived Dietary Adherence Questionnaire (PDAQ) adapted to the Benin Food Guide (53), dietary intake from the modified UKDDQ, and facilitator-rated behavioral monitoring (e.g., meal planning, food preparation, and physical activity practices) (51). Family functioning will be measured using the McMaster Family Assessment Device (54), diabetes knowledge using the ADKnowl questionnaire (55), and self-efficacy using the Diabetes Self-Efficacy Scale (DSES) (56). Anthropometric and clinical measures, including weight, height, waist circumference, blood pressure, and HbA1c—will also be collected with informed consent. Qualitative feedback from participants and facilitators will be analyzed to identify themes related to communication, comprehension, engagement, and perceived cultural relevance. Transportation incentives will be provided to facilitate participation in sessions and follow-up assessments.

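### Phase IIa tests convergent validity of the dietary adherence score against HbA1c and body measurements, which are not measures of diet, so the result cannot show whether the score measures diet (minor)

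*Protocol article*

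**What the plan says.** The Phase IIa analysis section (2.3.3) gives the validity check in one sentence: "Exploratory analyses will examine associations between dietary adherence scores and biomedical indicators (HbA1c and anthropometric measures) to assess convergent validity". The same section sets the significance level: "with statistical significance set at *P* < 0.05".

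The sample section (2.3.1) fixes the size, "A single-arm feasibility design will be used to enroll 30 adults with T2D", and requires that participants "have an HbA1c level >7% at enrollment". They come from the 512 people in Phase Ib, whose eligibility criteria (2.2.2) state no HbA1c threshold.

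The procedures section (2.3.2) sets the timing, "exploratory assessments of behavioral and biomedical outcomes will be conducted at baseline and 12 weeks post-intervention", and the measures: "Dietary adherence will be assessed using a multi-method approach combining the Perceived Dietary Adherence Questionnaire (PDAQ) adapted to the Benin Food Guide", together with intake from the modified UKDDQ and behavioral ratings made by facilitators. The three are to be combined. Neither 2.3.2 nor 2.3.3 states a comparison among them.

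**The concern.** The comparators do not fit the stated purpose. To show that a score converges, one compares it with another measure of the same thing. HbA1c and body size are measures of something else. Both also respond to influences other than diet, such as medication, disease duration and physical activity.

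This matters because the adapted PDAQ, the modified UKDDQ and the facilitator ratings carry forward into Phase IIb, where dietary adherence is the primary behavioral outcome. If the programme wants evidence in Phase IIa that the adherence score measures diet, the stated analysis will not supply it, whichever way the result falls.

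**Working it through.** **1. What the article says the comparators are.**
- Introduction and section 2.4.2: adherence is the primary behavioral outcome and glycemic control the primary biomedical outcome. They are two constructs.
- Section 2.1: better adherence is hypothesized to lead to better glycemic control. HbA1c is therefore downstream of adherence.
- Section 2.2.3: body mass index is an adjustment variable in the models relating family functioning, adherence and glycemic control. In section 2.3.3 anthropometry becomes a convergent indicator of adherence.

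The observed correlation between score and HbA1c depends on how well the score measures diet and on how strongly diet drives HbA1c. One correlation cannot separate the two.

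**2. Effect of the HbA1c entry rule on the baseline association.** The article gives no correlation, power or precision for this check, so there is no figure to reproduce. It also gives no HbA1c mean or SD. I assumed an unrestricted correlation r = 0.30 (in absolute value) and parent HbA1c means of 7.5–8.5 with SDs of 1.5–2.

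For normal HbA1c truncated below at 7, with a = (7 − mean)/SD and λ = φ(a)/(1 − Φ(a)):

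u = truncated SD / parent SD = √(1 + aλ − λ²)

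r′ = r·u / √(1 − r² + r²u²)

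- Mean 7.5, SD 2: a = −0.25, λ = 0.646, u = 0.65, r′ = 0.30 × 0.65 / √(0.91 + 0.09 × 0.42) = 0.20.
- Mean 8, SD 2: a = −0.50, λ = 0.509, u = 0.70, r′ = 0.21.
- Mean 8.5, SD 1.5: a = −1.00, λ = 0.288, u = 0.79, r′ = 0.24.

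The first and last of these are the extremes of the grid, so the range is 0.20–0.24. With right-skewed HbA1c (shifted gamma with lower bound 4 or 5, same means and SDs), u is 0.81–0.93 and r′ is 0.25–0.28.

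**3. Precision at n = 30.** Fisher z interval: tanh(atanh(r) ± 1.96/√27). Power is for a two-sided test at 0.05; the article does not state sidedness.

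| Correlation | 95% CI if observed | Power if true |
|---|---|---|
| 0.20 | −0.17 to 0.52 | 18% |
| 0.24 | −0.13 to 0.55 | 25% |
| 0.30 | −0.07 to 0.60 | 36% |

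An observed correlation must exceed 0.36 in absolute value to reach P < 0.05. At follow-up, retention of 75% (the article's feasibility benchmark) would leave about 23 people, and the threshold rises to 0.41.

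The sample size contributes at least as much as the entry rule: without any restriction, power at 0.30 is only 36%, and about 85 participants would be needed for 80%.

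**The case against.** The best defense is that this is mostly a matter of labelling. Checking whether a score relates to a variable that theory links to it is a recognized form of construct validation, some writers use the word convergent that broadly, and the article already calls the analysis exploratory. That stands in part: the associations are worth keeping. But the stated purpose is convergent validity, and they cannot deliver it.

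Three stronger readings are tempting and are not supported.

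- *A misleading result would cause a sound instrument to be dropped or a poor one kept.* The documents give no route for this. Progression rests on recruitment, retention, attendance, satisfaction and acceptability, and Phase IIb names the same three adherence measures without reference to this check.
- *The entry rule weakens the whole check.* It directly truncates HbA1c at enrollment only. Follow-up HbA1c can fall below 7%, and weight and waist circumference are affected only indirectly.
- *Comparing the diet measures with each other would be far better powered.* Any such contrast depends on assuming a larger correlation for that comparison. The article supplies no figure for either.

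It is also fair to say that a condensed article may leave cross-measure agreement to the full analysis plan. I therefore do not fault the omission as such. The point rests on the comparators that the article does name for this purpose.

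Finally, PDAQ against UKDDQ is not a perfect test. One asks about perceived adherence and the other supplies intake, and if both are self-reported, shared reporting error could inflate their correlation. HbA1c is free of that error. This calls for a caveat on the replacement; it does not make HbA1c a measure of diet.

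**Conclusion.** The point holds as a minor one. The mismatch between comparators and purpose follows from the article's own model and needs no assumption. It applies at both time points and to both HbA1c and anthropometry.

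The attenuation from the entry rule applies to the baseline HbA1c analysis. Its size rests on an assumed true correlation of 0.30 and assumed HbA1c distributions, and it is modest if HbA1c is skewed. The imprecision at 30 participants rests on the stated sample size. A weak or null association at baseline is therefore a likely result even for a valid score, and should not be read as evidence against it.

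**What to change.** In section 2.3.3:

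1. Define convergent validity as the baseline correlation, with its 95% confidence interval, between the adapted PDAQ and the modified UKDDQ. Note that shared self-report error may inflate it.
2. Add, as a secondary comparison, the correlation between the post-intervention PDAQ and the diet-related facilitator ratings, leaving out the physical activity items. These ratings are made during the intervention, so they cannot serve as a baseline comparator.
3. Keep the HbA1c and anthropometric analyses, but call them exploratory associations with clinical outcomes (hypothesis-testing construct validity). State that baseline HbA1c is restricted by the entry rule.

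The cost is a few sentences and one or two extra correlations on data already collected. At n = 30 the new correlations will also have wide intervals, so they should be reported as estimates and not as pass-or-fail tests.

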### Phase IIb: pilot study

2.4

Phase IIb will be conducted following completion of Phase IIa to evaluate the preliminary efficacy of the OSanDiaBé intervention compared with usual care among adults with T2D. Consistent with the ORBIT framework, this phase is designed to generate initial estimates of intervention effects on key behavioral and biomedical outcomes and to assess readiness for a subsequent, fully powered efficacy trial. Usual care consists of standard clinical management, including routine blood glucose monitoring, medication adherence counseling, and general lifestyle advice delivered in routine practice (57). We hypothesize that participants receiving OSanDiaBé will demonstrate greater improvements in dietary adherence and greater reductions in HbA1c at 6 months compared with those receiving usual care. We further hypothesize that these improvements will be maintained at 12 months following the end of active intervention contact.

#### Phase IIb sample

2.4.1

A total of 60 adults with T2D will be enrolled and randomized in a 1:1 ratio to either the intervention group (OSanDiaBé) or a wait-list control group receiving usual care. Randomization will be conducted after screening and informed consent using a computer-generated randomization sequence. To minimize potential bias, the principal investigator will be aware of group allocation, while physicians, data collectors, and laboratory personnel will remain blinded. Participants will be informed of their group assignment following randomization. The target sample size (*n* = 60; 30 per group) is consistent with recommendations for pilot randomized trials and is intended to support intervention refinement and effect size estimation for subsequent efficacy studies (58). Findings from Phase IIa will further inform final sample size considerations for later trials.

Participants will be recruited from six collaborating health centers using provider referrals, peer referrals, flyers, and word-of-mouth outreach. Eligibility criteria include: self-identification as Beninese; age 40–65 years; a clinical diagnosis of T2D for ≥1 year; uncontrolled diabetes (HbA1c >7%); availability of a supportive family member; and ability to provide written informed consent. Participants must be deemed suitable for group-based education and general dietary and lifestyle guidance by the referring healthcare provider. Exclusion criteria include pregnancy, recent major cardiovascular events (e.g., stroke or congestive heart failure), clinical conditions requiring specialized dietary management, or current participation in a similar nutrition program, to minimize contamination and ensure participant safety.

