#### Intervention manual refinement

2.2.2

Refinement of the OSanDiaBé intervention manual employed a mixed-methods approach combining quantitative surveys, FGDs, sensory evaluation, and stakeholder workshops. This approach was designed to assess feasibility, acceptability, and cultural relevance of intervention components; validate proposed menu plans; and inform the integration of key actors, particularly family members and dietitians, into intervention delivery.

**In the quantitative stage**, participants were recruited from outpatient diabetes units of six secondary health centers in Benin (two public and four private). Eligible participants were adults aged 40–65 years with a documented diagnosis of T2D for at least 1 year, self-identified as Beninese, and willing to provide informed consent. Individuals with severe health conditions that could limit their ability to complete questionnaires or participate in anthropometric or biological assessments were excluded. The selected age range reflects the population most affected by T2D and its complications in Benin and sub-Saharan Africa and reduced heterogeneity in dietary behaviors and disease management experiences during intervention development. Requiring a minimum diabetes duration of 1 year ensured participants had prior exposure to diabetes self-management education and dietary recommendations, allowing meaningful assessment of dietary adherence, family functioning, and culturally embedded practices relevant to intervention refinement.

A total of 512 eligible participants were enrolled, consistent with recommendations for exploratory and formative research (43). Data collection included validated measures of dietary adherence, family functioning and support, cultural identity, and sociodemographic characteristics (age, sex, marital status, education, employment, income, ethnicity, and diabetes duration). Anthropometric measurements (height, weight, waist and hip circumference) and laboratory assessment of glycemic control (HbA1c) were also conducted.

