#### Quantitative analysis: phase Ib

2.2.3

All quantitative analyses were conducted using Stata (version 19; StataCorp LLC, College Station, TX, USA). Consistent with the objectives of ORBIT Phase Ib, analyses were designed to inform intervention refinement rather than to test intervention effectiveness.

Descriptive statistics, including means and standard deviations for continuous variables and frequencies and percentages for categorical variables, were used to summarize participant sociodemographic characteristics, dietary adherence, family functioning, and glycemic control. These analyses provided foundational information to guide refinement of intervention content, delivery strategies, and participant engagement approaches.

To examine hypothesized pathways specified in the Phase Ia theoretical model (Figure 2), mediation and moderation analyses were conducted using structural equation modeling (SEM) (47). These analyses assessed relationships among family functioning, dietary adherence, and glycemic control to identify psychosocial mechanisms relevant to intervention development and prioritization of intervention components. All SEM models were adjusted for age, sex, education level, diabetes duration, body mass index, health center, marital status, work status, and social support, variables known to influence dietary adherence and glycemic control, to reduce potential confounding (48, 49).

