#### Quantitative analysis: phase IIb

2.4.3

All quantitative analyses will be conducted using Stata (version 19; StataCorp LLC, College Station, TX, USA). Normality of continuous variables will be assessed using the Kolmogorov–Smirnov and Shapiro–Wilk tests, with non-parametric methods applied as appropriate. Continuous variables will be summarized using means and standard deviations, and categorical variables using frequencies and percentages. Between-group comparisons will be conducted using Student's *t*-tests for continuous variables and chi-square tests for categorical variables. To examine changes in outcomes over time, repeated-measures analysis of variance (ANOVA) will be used to assess group-by-time interactions across baseline, 6-month, and 12-month assessments, with Bonferroni-adjusted *post hoc* comparisons. Models will adjust for baseline values of outcome measures. Statistical significance will be set at *P* < 0.05. Sensitivity analyses will be conducted using multiple imputation to address missing data and assess the robustness of findings.

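### Phase IIb describes no stratification by health center and adjusts only for the baseline outcome, although the article calls center influential: a cheap gain in precision is left unused

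*Protocol article*

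**What the plan says.** All references are to the protocol article.

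- **Size and allocation (2.4.1 Phase IIb sample):** "A total of 60 adults with T2D will be enrolled and randomized in a 1:1 ratio", that is, 30 per group. The size "is consistent with recommendations for pilot randomized trials and is intended to support intervention refinement and effect size estimation for subsequent efficacy studies".
- **Recruitment (2.4.1):** "Participants will be recruited from six collaborating health centers using provider referrals, peer referrals, flyers, and word-of-mouth outreach".
- **Randomization (2.4.1):** "Randomization will be conducted after screening and informed consent using a computer-generated randomization sequence". The text mentions neither strata nor blocks.
- **Comparator (2.4 Phase IIb: pilot study):** usual care is standard clinical management, described as including "general lifestyle advice delivered in routine practice".
- **Efficacy model (2.4.3 Quantitative analysis: phase IIb):** repeated-measures ANOVA for the group-by-time interaction. The only adjustment named is "Models will adjust for baseline values of outcome measures".
- **Formative phase (2.2.3 Quantitative analysis: phase Ib):** all structural equation models are adjusted for a list of nine variables that ends "health center, marital status, work status, and social support, variables known to influence dietary adherence and glycemic control".

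Section 2.4.2 makes dietary adherence and HbA1c the primary outcomes of Phase IIb. These are the same two outcomes that 2.2.3 says center influences.

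**The concern.** The article treats health center as prognostic for both primary outcomes when it analyzes the formative data. It then names a covariate set without center for its only randomized comparison, and gives no reason. With six centers and 60 people, each center supplies about ten participants if recruitment is even, so unstratified allocation will often leave individual centers unevenly split between arms.

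What is at stake is efficiency. Outcome variation between centers that is neither balanced by design nor modeled stays in the error term and widens the confidence interval. In a pilot of 30 per arm whose stated purpose includes estimating an effect size for later trials, precision is scarce and this part of it is inexpensive to recover.

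**Working it through.** **Plan's own figure.** No power calculation is stated, so the only figure to reproduce is 2 × 30 = 60, which agrees. For scale, with two-sided alpha 0.05 assumed, 30 per arm detects a standardized difference of (1.960 + 0.842) × √(2/30) = 0.72 with 80% power.

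**Inputs from the article:** N = 60, 30:30, six centers, baseline outcome the only covariate. **Assumed:** ten participants per center; share ρ of outcome variance (after baseline adjustment) lying between centers, 0.01 to 0.20; SD s of center effects on HbA1c, 0.3 to 0.5 points.

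**1. How often centers split unevenly without strata.** The number allocated to intervention in one center is hypergeometric (60 people, 30 intervention, 10 drawn).
- One given center 7:3 or worse: 0.299; 8:2 or worse: 0.080.
- At least one of six centers 7:3 or worse, by simulation: about 0.84; 8:2 or worse: about 0.37.
- With uneven recruitment (20, 15, 10, 5, 5, 5), at least one center has 70% or more in one arm in about 0.82 of allocations.

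**2. What imbalance contributes to the treatment effect.** The variance of the count in one center is 10 × 0.5 × 0.5 × 50/59 = 2.119. The variance of the arm difference due to center effects is s² × 6 × 4 × 2.119/30² = 0.0565 s², so the SD is 0.238 s.
- s = 0.3: 0.07 HbA1c points. s = 0.5: 0.12 points.

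**3. Standard error without strata and center term, relative to having both.** To a first approximation the ratio is 1/√(1 − ρ), ignoring the 5 degrees of freedom.

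| ρ | SE ratio | Power at d = 0.72 with center handled (80% without) |
|---|---|---|
| 0.01 | 1.005 | 80.4% |
| 0.05 | 1.026 | 82.0% |
| 0.10 | 1.054 | 84.0% |
| 0.20 | 1.118 | 87.9% |

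This formula weights center variance by 4/60 = 0.0667. Using the fixed-split weight 0.0565 from step 2, the ratio is √(1 + 0.8475 ρ/(1 − ρ)), which gives 1.004, 1.022, 1.046 and 1.101. The order of magnitude is the same.

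**4. Why design and model should change together.**
- *Center term without strata:* the expected R² of arm on center is 5/59 = 0.085. Six fixed center effects then inflate the standard error by about 1/√(1 − 0.085) = 1.045. By the formula in step 3, this pays only if ρ exceeds about 5/59, or 8.5%.
- *Strata without center term:* the reported standard error is too large. The true two-sided alpha falls from 5% to about 4.9%, 4.4%, 3.9% and 2.8% for ρ = 0.01, 0.05, 0.10 and 0.20.

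**The case against.** The case on the other side is substantial, and most of it stands.

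- **The article is silent on strata.** A reader might infer that the sequence is unstratified. The text does not say so, and a condensed article may leave strata and blocks to the full protocol. The covariates in 2.4.3, however, are stated, and center is not among them. If the full protocol does stratify, that model still lacks the matching term.
- **No bias follows.** A reader might infer that part of the treatment effect would reflect which clinic supplied the participants. Individual randomization rules this out in expectation. Chance imbalance is ordinary sampling error that the unadjusted standard error already covers. The 84% figure describes any one of six small groups; it says nothing about net distortion, because centers can offset one another.
- **Differing usual care is not documented.** Section 2.4 gives a single description of usual care. The mix of two public and four private centers is reported for Phase Ib in 2.2.2; nothing says that the Phase IIb centers are the same six.
- **The two covariate lists do not contradict each other.** Section 2.2.3 adjusts observational models against confounding, which a randomized comparison does not need. It also lists nine variables, and nobody would stratify 60 people on all nine. Center still differs from most of them in practice: it is a design factor, fixed and known at allocation, and the usual one to stratify on.
- **Baseline adjustment already helps.** Participants have had diabetes for at least a year, so baseline HbA1c probably carries persistent center differences. It cannot carry differences that arise during follow-up.
- **It is a pilot.** This lowers the stakes, though effect-size estimation is one of its stated aims.

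**Conclusion.** The point holds as a cheap improvement in precision. The article calls center influential on both primary outcomes, yet its only randomized comparison names no center stratification and no center term, and does not say why.

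The size depends on a between-center share that the article does not give. At an assumed 5–20% of variance, the standard error is about 3–12% larger than with stratification plus adjustment; near 1% there is nothing worth gaining. The 0.07–0.12 HbA1c points from an assumed center SD of 0.3–0.5 are a component of the total sampling error and should not be read as added error or bias. The imbalance figures also assume ten participants per center.

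The document does not support a claim that the comparison is confounded by clinic, or that the arms will receive different usual care.

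**What to change.** - **2.4.1 Phase IIb sample:** state that the computer-generated sequence is stratified by health center with randomly varied block sizes, or by public/private type if some centers are expected to enrol very few. If the full protocol already stratifies, say so here.
- **2.4.3 Quantitative analysis: phase IIb:** add the same stratification factor to the Phase IIb outcome models alongside the baseline value. If centers are small, use the coarser factor or a random center intercept in place of six fixed effects.

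Make both changes together. If center is left out deliberately, give the reason in view of 2.2.3.

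The cost is at most 5 degrees of freedom (from 60 − 2 = 58 to 53 in a simple two-arm comparison) and slightly more list management before the start. No extra patients or visits are needed.

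### The Phase IIb exclusion covers only current programme participation, so people already treated with OSanDiaBé in Phase IIa are not excluded from randomisation to either arm

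*Protocol article*

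**What the plan says.** Section 2.4.1 (Phase IIb sample) of the protocol article lists pregnancy, recent major cardiovascular events, conditions needing specialised dietary management and "current participation in a similar nutrition program, to minimize contamination and ensure participant safety" as exclusions. The last is the only one that concerns exposure to a programme. In the same section, "A total of 60 adults with T2D will be enrolled and randomized in a 1:1 ratio", to OSanDiaBé or to "a wait-list control group receiving usual care". The inclusion criteria cover Beninese identity, age 40–65, "a clinical diagnosis of T2D for ≥1 year; uncontrolled diabetes (HbA1c >7%); availability of a supportive family member" and written consent, and the referring provider must judge the person suitable. On recruitment: "Participants will be recruited from six collaborating health centers using provider referrals, peer referrals, flyers, and word-of-mouth outreach".

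Section 2.3.1 (Phase IIa sample) describes a single-arm study in which all 30 participants receive the intervention. On their source: "Participants will be recruited from the pool of 512 individuals who participated in Phase Ib". Section 2.2.2 says of that pool that "participants were recruited from outpatient diabetes units of six secondary health centers in Benin". Section 2.4 places Phase IIb after completion of Phase IIa.

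**The concern.** The exclusion exists to limit contamination, yet its wording turns on the word *current*. The people most directly exposed to the programme before Phase IIb are those who finished it in Phase IIa, and by then none of them is a current participant. No section shown excludes them, sets a washout, stratifies on prior exposure or adjusts for it.

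The estimate of effect is at stake. The Phase IIb sample size "is consistent with recommendations for pilot randomized trials and is intended to support intervention refinement and effect size estimation" for later trials. A participant who has already had most of the intervention supplies a smaller treatment contrast than an untreated one, whichever arm he or she is assigned to.

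**Working it through.** **Do Phase IIa graduates pass the Phase IIb screen?**

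| Criterion | Phase IIa (2.3.1) | Phase IIb (2.4.1) |
|---|---|---|
| Beninese identity | yes | yes |
| Age | 40–65 | 40–65 |
| T2D duration | at least 1 year | at least 1 year |
| HbA1c | >7% at enrolment | >7% |
| Family support | required | required |
| Earlier OSanDiaBé | not applicable | only current participation in a similar programme excluded |

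The shared criteria match. HbA1c must still exceed 7% at the new screening, so fewer than 30 may qualify. That screen acts on HbA1c alone. It does not remove graduates whose dietary adherence (the primary behavioural outcome), diabetes knowledge or self-efficacy has already improved.

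**How much have they received?** Phase IIa gives 2 individual + 8 group = 10 sessions. Phase IIb gives 4 + 8 = 12. A graduate has had as many sessions as 10 of the 12, including the full number of group sessions.

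**Effect on the contrast.** The article gives no effect size, SD or power for n = 60, so there is no stated figure to reproduce. The following is an illustration on assumptions.

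Let δ be the effect in untreated people and k the number of graduates among the 60, so that f = k/60 is their expected share of each arm. Let r be the fraction of δ that a graduate on usual care still holds at follow-up. Assume that repeat treatment brings a graduate back to δ and no further.

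- Comparing follow-up values: the intervention arm is at δ and the control arm at f·r·δ. The contrast is δ(1 − f·r).
- Comparing change from baseline: let a graduate enter with fraction r₀ of δ. In the intervention arm the graduate gains δ(1 − r₀), and in the control arm changes by δ(r − r₀). The difference is δ(1 − r). Averaged with untreated participants this is (1 − f)δ + f·δ(1 − r) = δ(1 − f·r).

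Both comparisons give the same expected dilution, f·r.

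| Assumed k | f = k/60 | Loss, r = 1 | Loss, r = 0.5 | Expected graduates among 30 controls | P(at least one in control) |
|---|---|---|---|---|---|
| 3 | 5% | 5% | 2.5% | 1.5 | 0.88 |
| 6 | 10% | 10% | 5% | 3 | 0.99 |
| 10 | 16.7% | 16.7% | 8.3% | 5 | >0.999 |

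The last column is 1 minus the hypergeometric probability of zero. For k = 3 it is 1 − (30·29·28)/(60·59·58) = 1 − 0.119 = 0.88. With r = 0 the loss is nil for every k.

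**Scale against sampling error.** For an assumed standardised effect of 0.5 with 30 per arm, the standard error is √(2/30 + 0.5²/120) = 0.26. A 16.7% loss shifts the effect by 0.5 × 0.167 = 0.083, or about 0.32 of a standard error.

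**The case against.** The strongest reply is that this is a condensed article. Its exclusion list is introduced by *include*, so a fuller protocol may bar earlier participants. The article does not say that re-enrolment is planned, nor that the six Phase IIb centres are the six of Phase Ib, although that is plausible. Phase IIb also uses its own recruitment routes instead of drawing on the 512. All of this stands and limits how firmly the consequence can be stated. It does not remove the point: the article states this criterion together with its purpose, and the wording misses the most directly exposed group.

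A second reply is that baseline adjustment absorbs the earlier effect, so graduates in the control arm do no harm. Adjustment moves the loss without removing it: graduates in the intervention arm then have less left to gain, and the expected dilution is the same, as shown above.

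A third reply is that full persistence is the extreme case. That is fair. Phase IIb adds two booster sessions and revised materials, and the HbA1c screen selects weaker responders. Some persistence is nevertheless the trial's own hypothesis: section 2.4 expects improvements to hold to month 12, six months after contact ends.

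A reader might go further and infer that graduates are likely volunteers, that they would pass programme content to other controls, or that a Phase III trial would need 1.44 times the sample. The documents support none of these. Nothing describes graduates' willingness to re-enrol, and controls share no sessions under the plan. The factor 1/(1 − 0.167)² = 1.44 assumes ten graduates, full persistence and a Phase III sized from this single point estimate.

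**Conclusion.** As written, the exclusion does not reach people who completed OSanDiaBé in Phase IIa. Those still above 7% HbA1c who meet the other criteria could be randomised to either arm, which defeats the rule's stated aim for that group. The harm is conditional. If k graduates re-enrol, keep their earlier benefit in full and gain nothing from repetition, the expected contrast falls by k/60 (5%, 10% or 17% for assumed k of 3, 6 or 10). It falls by about half as much with half persistence, and hardly at all if the benefit has waned. If repeat treatment did add benefit beyond δ, the dilution would be smaller still or could reverse, so a flat statement that the pilot is biased toward zero is not supported. The value of k is not in the documents. The likely shift is modest beside the sampling error of a 60-person pilot, but it is systematic and easily avoided.

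**What to change.** Reword the exclusion as: current or previous participation in OSanDiaBé (including Phase IIa) or in a similar nutrition programme. Check each person screened against the Phase IIa enrolment list. If the full protocol already has such a rule, state it in the article.

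The number of previously treated Phase IIa participants among those randomised is then zero by design, and n = 60 is unchanged. The cost is one line of text, a list check at screening, and the loss of at most 30 people from the catchment of six centres. Extending the exclusion to members of Phase IIa participants' households is optional. It has some rationale, because family members are invited to selected group sessions (section 2.3.2), but the main gap closes without it.
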